#### Vaccination during pregnancy

Pregnancy was an exclusion criterion for the past clinical trials in this program. A mandatory pregnancy test was performed before each vaccination and a commitment to use adequate contraception was requested from all females of childbearing potential. A minimal number of inadvertent pregnancies occurring during clinical trials with the Ebola candidate vaccines Ad26.ZEBOV, Ad26.Filo, and MVA-BN-Filo have been followed to term.

The most recent aggregate review of pregnancy exposure data was performed in August 2019. This analysis of the current experience with pregnancies after exposure to the Ebola candidate vaccines (Ad26.ZEBOV, Ad26.Filo, MVA-BN-Filo) in female study participants or partners of male study participants did not reveal a safety concern.

Serious complications/SAEs during pregnancy were reported in 24 out of a total of 79 pregnancies, i.e., in 20 women study participants and in 4 women partners of male study participants. None of these serious complications/SAEs were considered causally associated with the study vaccines by investigators and/or the company. No apparent concerning pattern of AEs is emerging from this review. No congenital malformations were reported to date to the company in fetuses or newborns. Spontaneous abortion was the most commonly observed SAE (11 out of 79 pregnancies) with an incidence of 13.9%, which is within the range of expected spontaneous abortion rates during the first trimester of gestation even when considering that spontaneous abortion incidences vary significantly depending on geographical areas and individual risk factors (e.g., age, previous abortions) [13–16].

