
#### Exclusion criteria

History of EVD (self-declared or laboratory confirmed)Has received any candidate Ebola vaccine (except for women found to be pregnant in the Umurinzi study after they receive their first vaccine dose, who are eligible for enrollment into a non-randomized group under this protocol)Has received any experimental candidate Ad26- or MVA-based vaccine in the past. Receipt of any approved vaccinia/smallpox vaccine or Ad-based candidate vaccine other than Ad26 at any time prior to study entry is allowedKnown allergy or history of anaphylaxis or other serious adverse reactions to vaccines or vaccine products (including any of the constituents of the study vaccines [e.g., polysorbate 80, ethylenediaminetetraacetic acid (EDTA) or L-histidine for Ad26.ZEBOV vaccine; tris (hydroxymethyl)-amino methane (THAM) for MVA-BN-Filo vaccine]), including known allergy to egg, egg products, chicken proteins, and aminoglycosidesParticipant with acute illness (this does not include minor illnesses such as diarrhea or mild upper respiratory tract infection) or body temperature ≥ 38.0 °C on day 1 will be excluded from enrollment at that time but may be rescheduled for enrollment at a later datePresence of significant conditions (e.g., history of seizure disorders, (auto)immune disease or deficiency, any spleen disease, active malignancy, ongoing tuberculosis treatment, other systemic infections) or clinically significant findings during screening of medical history, obstetric history, physical examination, vital signs or laboratory testing for which, in the opinion of the investigator, participation would not be in the best interest of the participant (e.g., compromise the safety or well-being) or that could prevent, limit, or confound the protocol-specified assessments. Participant who have recently received treatment for acute, uncomplicated malaria are eligible for participation if at least 3 days have elapsed from the conclusion of a standard, recommended course of therapy for malaria; subjects who are acutely ill with malaria at the time of screening should complete therapy and wait an additional 3 days after completion before screening for the study. Subjects with sickle cell trait can be includedDuring the 6 weeks prior to screening, have had ANY of (a) confirmed SARS-CoV-2 (COVID-19) infection (test positive), OR (b) suspected SARS-CoV-2 infection (clinical features without documented test results), OR (c) close contact with a person with known or suspected SARS-CoV-2 infectionHistory of or underlying liver or renal insufficiency, or significant cardiac, vascular, pulmonary (e.g., persistent asthma), gastrointestinal, endocrine, neurologic, hematologic, rheumatologic, psychiatric, or metabolic disturbancesHistory of hepatitis B surface antigen (HBsAg) or hepatitis C antibody (anti-HCV) positive, or other clinically active liver disease, or tests positive for HBsAg or anti-HCV at screeningHIV-infected but not on stable antiretroviral therapy, defined as adherent to ART regimen for ≥ 6 weeks prior to enrolment. HIV-infected subjects on stable ART may be enrolledObstetric history including:a ≥ 2 consecutive spontaneous abortionsbHistory of pre-eclampsia or eclampsiacRhesus negative multigravidadGrand multigravida (> 5 previous pregnancies)ePrevious late still birth (defined as loss of pregnancy at any time after 28weeks gestation)fPrevious low birth weight baby or premature delivery (defined as a delivery before 37weeks gestation)gPrevious neonatal death (defined as death of an infant within the first 28days of life)hPrevious delivery of an infant with a known or suspected genetic or chromosomal abnormalityiHistory of other significant pregnancy-related or neonatal complications judged likely to affect the safety of the mother or infant or to significantly compromise the endpoint data collected. Previous cesarean section is not an exclusion criterionMajor surgery within the 4 weeks prior to screening or planned major surgery through the course of the study (from screening until completion of the study)Chronic or recurrent use of immunomodulators/suppressors, e.g., cancer chemotherapeutic agents, systemic corticosteroids within 6 months before the planned administration of the first dose of study vaccine. Ocular, topical or inhaled steroids are allowedReceived or plan to receive a licensed non-live attenuated vaccine (e.g., tetanus) within 7 days of a study vaccination (i.e., before or after). Received or plan to receive licensed live attenuated vaccines within 4 weeks of a study vaccination (i.e., before or after)Received an investigational drug or investigational vaccine or used an invasive investigational medical device within 3 months prior to screening or current or planned participation in another clinical study during the study. Participation in an observational clinical study is allowedReceipt of blood products or immunoglobulin within 3 months prior to screening and/or during participation in the study (with the exception of RhoGAM)Current or past abuse of alcohol, recreational, or narcotic drugs which in the investigator’s opinion would compromise the subject’s safety and/or compliance with the study proceduresHistory of chronic urticaria (recurrent hives)Participant cannot communicate reliably with the investigatorEmployee of the investigator or study site, with direct involvement in the proposed study or other studies under the direction of that investigator or study site, as well as family members of the employees or the investigatorHistory of thrombotic thrombocytopenia syndrome (TTS) or heparin-induced thrombocytopenia and thrombosis (HITT)

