^p^If pregnancy completion/termination in a group B woman occurs prior to performing all in-pregnancy protocol visits, these missed visits will not be considered as protocol deviations

**Table 4 Tab4:** Schedule of activities—women From Umurinzi

Visit #	1	2	3	4	5	EE
**Visit timing**		**Dose 2**	**Dose 2 + 28 days**	**Pregnancy completion/termination**	**PP 1 + 42 days**	**Early** **exit**
**Visit day and window**	** − 28 to 1**	**D57** ** − 14 days, + 28 days**	**D85 ± 7 days**	**PP 1** ^a^ ** + 2 days**	**PP 43** ^b^ ** ± 14 days**	
**Visit type**	Screening	**Dose 2**	Safety	Safety and immuno	Safety	Early exit
Assessment of understanding	•					
Written informed consent (ICF) ^c^	•					
Inclusion/exclusion criteria	•					
Demographics ^d^	•					
Medical and obstetric history ^e^; pre-pregnancy and pre-study meds	•					
Physical examination ^e^	•				•	•
Obstetric exam ^e^	•	•		•		•^m^
Targeted physical exam ^e^		•	•			
Vital signs ^e^ incl. body temperature	•		•	•	•	•
Urine pregnancy test ^f^	•					
Hematology, chemistry ^f^	•					
Urine dipstick/urinalysis ^f^	•	•	•			
Syphilis, HIV, hepatitis B and C, malaria screening ^f^	•					
Obstetric ultrasound ^g^	•		•			•^m^
Biometric scan	•	•	•	•	•	•
Contact information	•	•	•	•	•	•
Pre-vaccination symptoms ^h^						
Vaccination		•				
30 min post-vaccination observation^i^		•				
Adverse maternal, fetal outcomes		•	•	•	•	
SAE recording		•	•	•	•	•
Concomitant medications ^j^	•	•	•	•	•	•
Delivery history ^k^				•		
Post pregnancy physical examination ^k^				•		
Laboratory assessments ^l^				•		

pre-dose;

pre- and post-dose

^a^PP 1 refers to the day of pregnancy completion/termination. Visit 4 (PP 1) should occur on the day of pregnancy completion/termination or within 2 days

^b^Visit 5 (PP 43) scheduled to occur at routine 6 week post-partum visit

^c^Must be signed before first study-related activity

^d^Maternal demographic information to be collected at screening includes: date of birth, race/ethnicity, education level, geographical location/residence, occupation, household size (number of persons living in the same home), and international travel history

^e^Information to be collected for medical and obstetric history, physical exams, and vital signs is specified in the protocol

^f^Urine dipstick for protein and glucose will be performed at these visits. If results are 1 + or greater, additional work-up for pre-eclampsia and gestational diabetes may be warranted

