## Statistical methods

### Statistical methods for primary and secondary outcomes {20a}

For purposes of analysis, the following populations are defined:Full analysis set (FAS): The FAS will include all randomized participants. All safety analyses will be made on the FASPer-protocol immunogenicity (PPI): The PPI population will include all randomized and vaccinated participants for whom immunogenicity data are available excluding participants with major protocol deviations expecting to impact the immunogenicity outcomes

Of note, women enrolled from Umurinzi will be analyzed separately. No formal statistical testing is planned. The number and percentage of participants screened, enrolled, randomized, receiving two vaccine doses, and completing follow-up will be summarized by study arm.

Baseline demographic characteristics (including gestational age and obstetric risk assessment) will be tabulated overall and by study arm.

The frequency and percentage of women for whom at least one of the indicated adverse outcomes was reported as a primary endpoint (see above) will be summarized by study group. For each separate adverse maternal/fetal and adverse neonatal/infant outcome, the number and percentage of participants who experience at least 1 occurrence of the given event will also be tabulated by study group (groups A and B, and their infants). The verbatim terms used in the CRF by investigators to identify AEs will be coded using the Medical Dictionary for Regulatory Activities (MedDRA). The reporting of the categorical safety data will include the incidence, severity, relatedness, and type of AEs. Continuous safety parameters will be analyzed descriptively (showing the mean, standard deviation, median, and quartiles [Q1 and Q3]).

For participants from group A, all reported AEs, events-related diary information (solicited local at injection site and systemic, and unsolicited) with onset within 4 weeks post dose 1 or dose 2 vaccination (i.e., treatment-emergent AEs) will be included in the analysis. For each AE, the number and percentage of participants who experience at least 1 occurrence of the given event will be summarized. Of note, solicited and unsolicited AEs will not be collected for group B participants.

Summaries, listings, datasets, or participant narratives may be provided, as appropriate, for those participants who die, who discontinue intervention due to an AE, or who experience a severe or a serious AE.

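### Table 4 gives already-vaccinated Umurinzi women the randomized groups' timing: the screening window contradicts eligibility, the risk period has no valid start, and a simple spontaneous abortion percentage understates risk since dose 1

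*Protocol article*

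**What the plan says.** The Exclusion criteria make one exception to the bar on earlier Ebola vaccination: "women found to be pregnant in the Umurinzi study after they receive their first vaccine dose, who are eligible for enrollment". They enter a non-randomized group. Their schedule is Table 4, "Schedule of activities—women From Umurinzi".

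- **Timing in Table 4.** Visit 1 is screening, with window -28 to 1. Visit 2 is dose 2 at D57 (-14, +28 days). Visit 3 is 28 days later, at D85. Visit 4 is the end of pregnancy and visit 5 follows about six weeks after.
- **Recording in Table 4.** Consent is taken at visit 1 ("Must be signed before first study-related activity"). The row "Adverse maternal, fetal outcomes" is marked at visits 2 to 5. The row "SAE recording" is marked at visits 2 to 5 and at early exit. Neither is marked at visit 1.
- **Endpoints (Table 1).** Maternal/fetal outcomes and maternal SAEs are counted from randomization.
- **Eligibility.** The Inclusion criteria require a singleton pregnancy confirmed at screening.
- **Analysis.** Statistical methods {20a} restricts the full analysis set to randomized participants and says that "women enrolled from Umurinzi will be analyzed separately".
- **The only spontaneous abortion rate given.** Under Vaccination during pregnancy: "Spontaneous abortion was the most commonly observed SAE (11 out of 79 pregnancies) with an incidence of 13.9" per cent. It comes from inadvertent pregnancies in other trials of the vaccines, not from this group.

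**The concern.** In Tables 2 and 3, leaving outcomes and SAEs unmarked at screening is sound. No woman is randomized before visit 2, and a group A woman is unexposed until then. Table 4 has the same pattern, but its visit 2 is dose 2 and every woman has been exposed since dose 1. The window label has the same form as in the other tables, although day 1 is already past for anyone who qualifies.

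This group bears on the label question. Umurinzi vaccinates non-pregnant people (Background and rationale), so a pregnancy found after dose 1 was probably very early, or not yet conceived, at that dose. The Discussion expects only 1.5% to 4.25% of recruits to enter in the first trimester, so early-exposure data are scarce elsewhere in the study. A loss percentage from this group could easily be read as risk after early exposure, although it describes only women still pregnant when they enrolled.

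**Working it through.** **1. Screening window against eligibility.** Dose 2 at D57 is 57 - 1 = 56 days after D1, the 8-week interval, so D1 is the day of dose 1. Visit 3 at D85 fits, being 28 days after D57. On that scale a window of -28 to 1 ends on the day of dose 1. Women qualify only if found pregnant after dose 1. The two statements cannot both hold.

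If the label is instead meant to count back 28 days from dose 2, nominal screening falls between D57 - 28 = D29 and D57. That is compatible with eligibility, but Table 4 does not say so, and its other pre-delivery visits use the dose 1 scale.

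**2. Time from dose 1 to the first marked recording visit.**
- Earliest: 57 - 14 - 1 = 42 days
- Nominal: 57 - 1 = 56 days
- Latest: 57 + 28 - 1 = 84 days

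**3. How much of this can follow consent.** On the reading that counts from dose 2, at most 28 days.

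| Dose 2 after dose 1 | At most after consent | Before earliest consent |
|---|---|---|
| 42 days | 28/42 = 67% | 14 days |
| 56 days | 28/56 = 50% | 28 days |
| 84 days | 28/84 = 33% | 56 days |

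The last column is closed to any change in recording: a woman who loses the pregnancy in that time cannot be enrolled.

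**4. Left truncation, as an illustration.** The plan's figure reproduces: 11/79 = 13.9%. Assume, for illustration only, that this is the total risk after dose 1, and that a share f of the loss hazard falls before observation starts. With H = -ln(1 - 11/79) = 0.150, the risk seen from dose 2 is 1 - exp(-H(1 - f)). If observation starts at consent with 28 of 56 days gained, and the early hazard is even over the interval, f becomes f/2.

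| Assumed f | Seen from dose 2 | Seen from consent |
|---|---|---|
| 0.25 | 10.6% | 12.3% |
| 0.50 | 7.2% | 10.6% |
| 0.75 | 3.7% | 8.9% |

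Every entry is below 13.9%. Starting at consent narrows the gap but does not close it. The protocol gives no value for f, no size for this group and no gestational age at dose 1, so the table shows direction, not size.

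**5. Where an event between consent and dose 2 would go.** Visit 4 is timed to the end of pregnancy, not to dose 2, and both rows are marked there. Visit 2 and early exit record SAEs. Footnote p of Table 2 sets out what happens when a group A pregnancy ends before dose 2. Table 4 prints no counterpart.

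**The case against.** The strongest reply is that nothing after consent is shown to be missed. A loss between consent and dose 2 calls for visit 4, where outcomes and SAEs are both marked. Adverse event reporting {22} also requires all adverse events to be recorded, and hospitalizations during participation to be reported as SAEs, with listed exceptions. This stands. A reader might infer from the blank cells that such events go uncounted. The documents support only that the start of recording is unstated and ill-suited to this group.

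Losses between dose 1 and enrolment are absent because entry needs an ongoing pregnancy. That also stands: it is a selection effect, which reporting must address.

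A reader might also expect the group to look falsely reassuring beside groups A and B. That is not shown. Those groups must also be pregnant at entry, and few are expected to enter in the first trimester, so they too are left-truncated, mostly at a later gestation. If dose 1 fell at gestational week 2 to 4 (an assumption), dose 2 would fall at week 2 + 6 = 8 to week 4 + 12 = 16. Umurinzi women could then show more losses than the randomized groups.

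The window may be meant relative to visit 2, and the analysis detail may lie in the SAP. Either is possible. Neither removes the conflict in the printed day scale, nor supplies a start for endpoints tied to randomization.

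**Conclusion.** The point holds as a fault in the printed schedule and as a limit on how this group's losses can be read.

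- The screening window conflicts with the eligibility exception.
- The first marked outcome and SAE visit is 42 to 84 days after dose 1, rather than at consent, and the endpoint start does not exist for these women.
- A simple percentage with spontaneous abortion understates risk since dose 1. This rests only on the entry condition and on some losses occurring before enrolment. Its size cannot be derived from the protocol.

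It would go too far to call the group's SAE rate too low. The direction there is uncertain, and whether Umurinzi itself captured SAEs after dose 1 is not stated. A rate plainly labelled as running from dose 2 would not be wrong in itself. The group is descriptive, analyzed apart and outside the full analysis set, so the results for groups A and B are untouched.

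**What to change.** 1. In Table 4, start both recording rows at consent (visit 1).
2. State the reference day of the screening window and reconcile it with the exception in the Exclusion criteria.
3. State that outcomes and SAEs are recorded at visit 4 when a pregnancy ends before dose 2, as footnote p of Table 2 provides for group A.
4. In Statistical methods {20a}, report Umurinzi pregnancy losses as conditional on being pregnant at enrolment, by gestational age at entry (delayed entry). Say that they are neither risk since dose 1 nor directly comparable with groups A and B or with the 13.9%.

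The cost is two marks, a corrected label, a footnote and a sentence or two. The downside is small: a few more events to record, and a less favourable or more qualified rate.

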#### Sample size {14}

The primary outcomes of this unpowered study are adverse maternal, fetal, and neonatal/infant outcomes in vaccinated pregnant women and their neonates. The sample size was determined based on feasibility and estimated background incidence of the primary study outcomes. Background rates for adverse maternal and fetal outcomes in pregnancy are not comprehensively available for Rwanda for all events of interest. However, the Rwanda Demographic Health Survey (2014–2015) [16] provides rates of maternal death (210 per 100,000 live births) and neonatal death (20 per 1000 live births). With the proposed sample size of 1000, the probability of observing at least 1 AE occurring at a rate of 1/1000 is 63%. If no (S)AE (this includes adverse maternal/fetal outcomes) is observed in the vaccine group (*N* = 1000), this would provide 95% confidence that the true incidence is no more than 0.3%.

### Recruitment {15}

Pregnant women will be recruited from antenatal care (ANC) clinics. Recruitment will be conducted with residents of the catchment areas of the participating District Hospitals in Rwanda. Recruited women will be referred to the study sites located within the two District Hospitals for all study procedures.

## Assignment of interventions: allocation

### Sequence generation {16a}

Randomization will be used to minimize bias in the assignment of participants to group A or B, to increase the likelihood that known and unknown participant attributes are evenly balanced across both groups. An allocation template was created using Microsoft Excel. A total of 1051 sequentially numbered rows were created (1–1051), and for each row, a random number between 0 and 1 was generated. All rows with a random number less than or equal to 0.5 were allocated to group A and all rows with a random number greater than 0.5 were allocated to group B. Each site-specific set of 1051 sealed randomization envelopes will be securely stored at the appropriate site.

### Concealment mechanism {16b}

The allocation table is not visible to the trial staff conducting the randomization; therefore, the group assignment within each numbered envelope will be unknown to both participants and staff until each envelope is opened. Envelopes used for randomization are security-type (featuring a printed tint pattern inside the envelope to prevent contents from being read through a sealed envelope). The cards and envelopes will be prepared by the study team and inspected separately by 2 other members of the study team to ensure exact correspondence to the allocation table prior to sealing the envelopes and deploying them to the sites.

### Implementation {16c}

The allocation table was created by [name] at Emory University. Trained study investigators or study staff will enroll participants. Participants will be invited to reach into the bin to select a single sealed envelope containing a randomization assignment at the time of enrollment. Study staff will supervise this process to ensure that only one envelope is selected and opened. Once the envelope has been opened and the randomization card revealed, the randomization assignment will be complete and irreversible. Randomization of subjects will be documented in the Redcap Cloud clinical database by study staff.

## Assignment of interventions: blinding

### Who will be blinded {17a}

There will be no blinding in this study. Since the study vaccines have been judged to be of potential benefit to non-pregnant adults in the community through the Umurinzi campaign, an open-label design was selected for this trial to minimize the delay to vaccination for the control group.

